##### Immediacy of rewards

Research shows that reinforcement works best when the target behavior is followed by the reinforcer without delay
[37]. Delayed rewards are discounted, and a smaller amount given now is valued the same as a larger amount given later. In substance abusers, rewards are about twice as effective when they are delivered immediately, during the same clinic visit, than when the payment is delayed
[7]. Thus, we will pay rewards immediately after conducting the cotinine and CO tests, during visits at our center. This is why we will use NicAlert tests strips that produce results within a few minutes
[27].

##### Escalation and reset

Research shows that escalating systems produce longer periods of smoking abstinence compared with constant rewards
[38]. Because we want to reward sustained abstinence rather than initial quit attempts, we will use an escalating scheme and give incentives six times during 6 months (100, 150, 200, 300, 350, and 400 CHF at 1, 2, 3 weeks and at 1, 3, and 6 months, respectively). If people smoke or miss an assessment, the value of the next reward will be reset to the value of the last reward they attained, and the escalation scheme will start again at this value. Incentives will be paid only to people with negative CO and cotinine in saliva, assessed with NicAlert tests strips, and to NRT users who have positive cotinine tests but negative CO tests
[27].

### Behavioral intervention for both study groups

#### Quitter contract with quit date

A contract will be signed by each study participant, and countersigned by the research assistant and by the optional social supporter. In this contract, participants will commit to quit at a target quit date set no later than 1 month after enrolment, and to make additional quit attempts at a later date if the first quit attempt fails.

#### Social supporter

Participants who agree will designate a social supporter, preferably a non-smoker, with whom they have a regular, positive association (for example, spouse, friend, or colleague). Social supporters will countersign the participant’s quit contract. Social supporters will sign a consent form, receive a document describing their role in the study, and answer a brief questionnaire to return to us by mail, about their smoking status, age, sex, and address.

#### Internet-based, automatic behavioral support (‘Coach’)

Participants in both study groups will have the opportunity to enrol in an online ‘Coach’, which is an automatic, interactive, smoking cessation program. The ‘Coach’ consists of individually-tailored feedback reports, personal pages with progress graphs and a series of e-mail messages sent automatically over 3 months
[3,39]. Participants will also be encouraged to use the other services available on the Stop-tabac.ch website (discussion forums, ‘chats’, testimonials, fact sheets, and so on).

There will be no in-person behavioral support of telephone support. However, participants will be able to call the study assistant for administrative purposes.

#### Booklets

Participants in both the intervention and the control group will receive a series of self-help booklets
[3,40]. Finally, we will inform participants if any new, effective treatment of tobacco dependence is discovered during the study.

### Control group procedures

After randomization, participants in the control group will be informed about their group assignment, during the enrolment visit. They will be advised to quit smoking and will be encouraged to use the Stop-tabac website and self-help booklets in the same manner as the intervention group. They will be contacted again only for the follow-up surveys and for the cotinine, CO, and thiocyanate tests after 3, 6, and 18 months. In follow-up surveys, we will ask participants in both study groups whether they obtained smoking cessation support, and the type and amount of support they obtained (Internet, quitline, smoking cessation clinic, physician, medications, and so on). In data analyses, this will enable us to control for the amount of support received by participants.

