## Methods/design

### Objectives

The objective is to test whether a smoking cessation program combining financial incentives with Internet-based, individually-tailored behavioral support improves smoking cessation rates in low-income smokers, compared with cessation rates observed in a no-incentives control group, and to measure the size of this effect, 12 months after the incentives are stopped, that is, 18 months after the intervention starts. The secondary objectives are: to study whether the outcome is influenced by the characteristics of participants: age, sex and education, tobacco dependence level, motivation to quit (intrinsic/extrinsic
[26]), and smoking history; to assess the effect of financial incentives on quit attempts; and to assess whether financial incentives improve use of the online smoking cessation program.

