#### Follow-up after 3, 6, and 18 months

Participants will automatically receive by e-mail a request to answer the online follow-up questionnaires, 3, 6, and 18 months after their target quit date. After six e-mail reminders sent every 3 days, non-respondents to the online surveys will receive the follow-up questionnaires by postal mail. After three reminders by postal mail, non-respondents will be contacted by phone
[43]. The telephone survey in non-respondents will cover only a minimal subset of questions (smoking status, quit attempts, quit date and cigarettes/day). After six unsuccessful tries to reach non-respondents by phone at different hours and days of the week, we will contact a next of kin or a friend (whose address was provided at baseline by participants who agree with this procedure) to locate non-respondents. In our previous trials, this procedure enabled us to obtain response rates of about 95%
[40,44].

There is a risk that participants in the control group will drop out of the study when they learn about their group allocation, which would represent a threat to the validity of the study. We will make sure we obtain similarly high response rates in both study groups at follow-up.

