### Statistics

The main analysis will be a comparison of the proportions of abstinent smokers in the intervention and control groups. We will use chi-square tests and odds ratios with 95% confidence intervals to compare these proportions. If covariates are needed due to imbalance despite randomization, we will use multivariate logistic regression models instead. We will conduct subgroups analyses, and will use multivariate models to test whether the outcome is influenced by participants’ characteristics. We will assess whether motivation (intrinsic or extrinsic) acts as a mediator in the association between incentives and behavior
[26]. Analyses will compare participants who did or did not have a social supporter, or who did or did not use the online Coach, to see if these influence outcome or interact with treatment assignment.

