#### Sample size calculation

Based on our previous research in a similar population, we expect a quit rate of about 10% in the control group
[39,45]. Previous research showed that financial incentives either have little long-term effect on smoking cessation
[8], or an effect size of 0.31 to 0.48
[5,7], but larger incentives have a substantial effect (odds ratio > 3)
[6]. A sample size of 800 participants (2 x 400) will enable us to detect a difference between quit rates of 10% in the control group and 17% in the intervention group (odds ratio = 1.84, power = 80%, *P* = 0.05).

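### Adjusting for support received and testing Coach use as an effect modifier both condition on post-randomisation variables, so neither analysis would estimate the randomised effect of incentives

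*Protocol article*

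**What the plan says.** Under Control group procedures, the protocol article asks both arms in the follow-up surveys what type and amount of cessation support they obtained, and it counts Internet support among the types. It then states the purpose: "In data analyses, this will enable us to control for the amount of support received by participants".

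The Statistics section adds a comparison of participants "who did or did not use the online Coach, to see if these influence outcome or interact with treatment assignment". Coach enrolment is offered to both arms as an option (Internet-based, automatic behavioral support), so use of it develops during the trial.

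The Objectives section includes a secondary aim "to assess whether financial incentives improve use of the online smoking cessation program", and Assessment of efficacy lists use of that programme as a secondary outcome.

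The main analysis is a chi-square comparison of abstinence proportions with an odds ratio. All randomised participants are in the denominator and missing values count as smoking (Statistics; Intention-to-treat, missing data). Logistic regression replaces it if imbalance calls for covariates; the text does not say which variables qualify.

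On follow-up by telephone: "The telephone survey in non-respondents will cover only a minimal subset of questions". The items listed there are smoking status, quit attempts, quit date and daily cigarettes.

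**The concern.** One quantity, use of the online programme, has three roles: an outcome of incentives, part of the support to be controlled for, and a variable that defines subgroups for the treatment comparison. These roles conflict.

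If incentives raise use and use helps people quit, holding use constant removes the part of the effect that runs through it. If something unmeasured, such as determination to quit, drives both use and quitting, then users in the two arms are no longer comparable, and neither are non-users. An arm difference can then appear or shift even where incentives do nothing.

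At stake is how the secondary results are read. A support-adjusted odds ratio could be taken for a cleaner estimate of the incentive effect, and a Coach-by-arm interaction for evidence of who benefits. Neither reading would have the protection of randomisation.

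**Working it through.** **1. The plan's own figure.** Inputs from Sample size calculation: "10% in the control group and 17% in the intervention group", 400 per arm, 80% power, P = 0.05 (taken as two-sided).
- Odds ratio = (0.17/0.83)/(0.10/0.90) = 1.84, as stated.
- n per arm = [1.960·√(2·0.135·0.865) + 0.842·√(0.10·0.90 + 0.17·0.83)]² / 0.07² = 373 without continuity correction and 401 with it. Power at 400 per arm with the correction is 79.9%.

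The stated 2 x 400 reproduces. It rests on the unadjusted contrast, so nothing below changes it.

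**2. Removing part of the effect.** The documents give no uptake rates and no effect of support on quitting, so these are assumptions: use is 20% in controls and 40% with incentives; use has odds ratio 2 for quitting in both arms; control quit rate 10%; no common cause.
- Controls: 8.56% quit among non-users and 15.77% among users (odds ratio 2). Check: 0.8 × 8.56 + 0.2 × 15.77 = 10.0%.
- Incentives, with an odds ratio of 1.56 at fixed use: 12.74% and 22.60%. Overall: 0.6 × 12.74 + 0.4 × 22.60 = 16.7%.
- Total odds ratio = (0.1668/0.8332)/(0.10/0.90) = 1.80. The support-adjusted model reports 1.56.

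At the design effect (10% against 17%, total 1.84), the incentive-arm rates are 13.00% and 23.00%, since 0.6 × 13.00 + 0.4 × 23.00 = 17.0%. The adjusted odds ratio is (0.1300/0.8700)/(0.0856/0.9144) = 1.60.

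**3. Range of assumptions, total odds ratio held at 1.84.** The common cause here is binary and unmeasured, with odds ratio 3 on both use and quitting.

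| Use, control to incentive | Odds ratio of use for quitting | Common cause | Adjusted odds ratio |
|---|---|---|---|
| 40% to 50% | 2 | no | 1.73 |
| 40% to 60% | 2 | no | 1.62 |
| 40% to 60% | 2 | yes | 1.55 |
| 30% to 60% | 3 | yes | 1.26 |
| 40% to 60% | 1 | yes | 1.75 |
| 40% in both arms | 2 | no / yes | 1.86 / 1.87 |

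In the last row there is no attenuation. The small rise above 1.84 is the usual non-collapsibility of the odds ratio.

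**4. A true null.** Assume neither incentives nor use affects quitting, 10% quit in both arms, and a standard normal common cause acts on both use and quitting.
- Use 20% and 40%, log-odds 1 per SD: non-users quit at 8.36% (control) and 7.18% (incentive), users at 16.57% and 14.22%. Margins: 0.8 × 8.36 + 0.2 × 16.57 = 10.0% and 0.6 × 7.18 + 0.4 × 14.22 = 10.0%. Adjusted odds ratio 0.84; among users alone about 0.84.
- Same, with log-odds 0.5: 0.95.
- Use 20% and 30%, log-odds 1: 0.92.
- Equal use in both arms: exactly 1.00.

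The binary common cause of step 3 (use 40% to 60%) also gives 0.95 under the null.

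**5. Who would be in a support-adjusted model.** Neither description of the telephone survey (Allocation concealment; Follow-up after 3, 6, and 18 months) includes a support item. Telephone respondents would therefore lack the covariate, as would the 5% expected to be missing altogether (0.05 × 800 = 40). The share reached by telephone is not given. The same cannot be said of Coach use, because the documents do not say that it is self-reported.

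**The case against.** The strongest reply is that the main result is protected. It is an unadjusted comparison on all randomised participants, and no passage puts support received into it. That stands.

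A reader might infer that the imbalance clause lets support received into the main analysis. The wording does not exclude it, but imbalance despite randomisation most naturally means chance imbalance at baseline, and the Statistics section never mentions support received. The clause needs tightening; it does not show that the main analysis is biased.

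A reader might also infer that the protocol hypothesises an effect of incentives on all support. The explicit objective and outcome concern the online programme only. For quitlines, physicians or medication there is only the general rationale in Background and Rationale that incentives raise participation in treatment and use of its other components.

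It is fair, too, that the support sentence describes what the data will make possible and names no model, that the Coach comparison is not presented as the incentive effect, and that a condensed article leaves model details to an analysis plan. But both analyses are stated here in terms that conflict with the article's own outcomes, so this is more than an omission.

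Finally, the magnitudes are assumed, and a null effect is not distorted in every case: in step 4 it requires both a common cause and a change in use.

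**Conclusion.** The point holds for the secondary analyses. Support received and Coach use arise after randomisation, and use of the online programme is by the protocol's own account a possible result of the incentives. An incentive effect adjusted for them, or compared across their levels, is not the randomised effect. The primary intention-to-treat comparison, the sample size and the power are untouched.

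The size cannot be derived from the documents. If incentives raise use and use helps quitting, the adjusted odds ratio lies below the total: about 1.56 against 1.80 in the worked case, and 1.73 down to 1.26 against 1.84 over the wider range. Under a null with a common cause it is about 0.84 to 0.95. If incentives leave use unchanged, neither distortion arises. A support-adjusted model would in addition depart from the all-randomised denominator unless the missing support values are imputed. This should be fixed, but it does not threaten the main conclusion.

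**What to change.** - Control group procedures: delete the sentence on controlling for support, or relabel it as descriptive.
- Statistics: state that covariates used for imbalance, and variables used in subgroup or interaction tests of the treatment effect, are limited to those fixed before randomisation.
- Report support received and Coach use by arm as outcomes, which serves the existing objective on programme use.
- Label any analysis that conditions on either variable as exploratory, or as mediation with its assumptions stated (the Statistics section already names motivation as a possible mediator), and say how missing support data are handled.

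The cost is wording only; data collection, sample size and power do not change. What is lost is the Coach-by-treatment interaction as a result about effect modification.

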### Cessation induction *vs.* aid to cessation

Financial incentives may have two types of effects: they may induce quit attempts in people who would not otherwise have tried to quit (cessation induction); and they may increase the success of quit attempts (aid to cessation)
[41]. Since all participants will commit to make a quit attempt and set a quit date within 1 month of enrolment, our trial will not be a good test of cessation induction, it will rather be an aid-to-cessation trial. We will nevertheless assess the effect of the intervention on quit attempts, as a secondary outcome.

### Assessment of efficacy

The primary outcome will be continuous smoking abstinence between 6 and 18 months, that is, self-report of no puff of tobacco in the previous 7 days at 6 months plus self-report of no smoking between the 6- and 18-month surveys, not contradicted by CO, cotinine, and thiocyanate measurements. The date for follow-up surveys will be tied to the target quit date set at baseline.

As secondary outcomes, we will also assess:

Biochemically confirmed point prevalence of abstinence after 3, 6 and 18 months.

Abstinence at 3, 6, and 18 months using the ‘Russell Standard’, a recently suggested standard for smoking cessation trials
[42].

Quit attempts during the intervention phase (number, duration and dates).

Cigarette consumption, motivation to quit, confidence in ability to quit.

Use of the online smoking cessation program.

### Methods for assessing and recording efficacy parameters

To avoid using paper, questionnaires will be collected online. In non-respondents to the online surveys only, questionnaires will be collected by postal mail and then by phone.

#### Baseline data

After answering the online baseline questionnaire, participants will visit our center in Geneva, where smoking status will be biochemically verified. No smoking cessation counseling will be provided during the enrolment visit.

#### Follow-up after 3, 6, and 18 months

Participants will automatically receive by e-mail a request to answer the online follow-up questionnaires, 3, 6, and 18 months after their target quit date. After six e-mail reminders sent every 3 days, non-respondents to the online surveys will receive the follow-up questionnaires by postal mail. After three reminders by postal mail, non-respondents will be contacted by phone
[43]. The telephone survey in non-respondents will cover only a minimal subset of questions (smoking status, quit attempts, quit date and cigarettes/day). After six unsuccessful tries to reach non-respondents by phone at different hours and days of the week, we will contact a next of kin or a friend (whose address was provided at baseline by participants who agree with this procedure) to locate non-respondents. In our previous trials, this procedure enabled us to obtain response rates of about 95%
[40,44].

There is a risk that participants in the control group will drop out of the study when they learn about their group allocation, which would represent a threat to the validity of the study. We will make sure we obtain similarly high response rates in both study groups at follow-up.

#### Biochemical verification

The outcome is self-reported prolonged abstinence that is not contradicted by biochemical tests of recent abstinence. After 3, 6, and 18 months, participants who report abstinence (no puff of tobacco in the previous 7 days) will be invited to come to our center to perform a CO test and provide saliva samples for cotinine analysis and, if necessary, thiocyanate analysis. The procedure described above (multiple reminders by e-mail, postal mail, and telephone) will also be used to invite participants for the biochemical tests. After the reminders, a study assistant will offer to smokers who claim abstinence but do not show up for testing to meet them at their home or workplace or at a public space, to collect the CO and saliva samples. The saliva samples will be destroyed after the cotinine and thiocyanate analyses.

### Statistics

The main analysis will be a comparison of the proportions of abstinent smokers in the intervention and control groups. We will use chi-square tests and odds ratios with 95% confidence intervals to compare these proportions. If covariates are needed due to imbalance despite randomization, we will use multivariate logistic regression models instead. We will conduct subgroups analyses, and will use multivariate models to test whether the outcome is influenced by participants’ characteristics. We will assess whether motivation (intrinsic or extrinsic) acts as a mediator in the association between incentives and behavior
[26]. Analyses will compare participants who did or did not have a social supporter, or who did or did not use the online Coach, to see if these influence outcome or interact with treatment assignment.

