### Data

#### Questionnaires

The questionnaires will be collected online, and for non-respondents to the online surveys, by postal mail and over the phone. The questionnaires will be brief and focused, in order to maximize participation. Four waves of questionnaires will be collected in both study groups: at baseline and after 3, 6, and 18 months.

The baseline questionnaire will cover:

Age and sex, school years, occupation, income, body weight and height.

Smoking status, cigarette consumption, level of tobacco dependence.

Motivation to quit (intrinsic/extrinsic)
[26], past quit attempts, planned quit date.

Current and past use of smoking cessation treatments and medications.

Address, phone number, e-mail, Internet access.

The follow-up questionnaires (after 3, 6, and 18 months) will cover:

Smoking status (any smoking in the past 7 days, 4 weeks, 6 and 12 months).

Quit date in ex-smokers.

In current smokers: cigarette consumption and level of dependence.

Quit attempts (number, duration, dates).

Motivation to quit (intrinsic/extrinsic), confidence in ability to quit.

Smoking cessation treatments used since enrolment.

Opinions, satisfaction with the intervention.

Items bought with the gift cards by quitters in the intervention group.

Body weight.

Participants will automatically receive an e-mail message inviting them to take part in the online follow-up surveys, 3, 6, and 18 months after their target quit date. Participants who report that they have not smoked any tobacco in the past 7 days will be invited to make an appointment within the next days for biochemical verification.

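### Observed baseline imbalance decides whether the primary analysis is an unadjusted chi-square or an adjusted logistic model, so the primary test and the meaning of its odds ratio are not fixed in advance

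*Protocol article*

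**What the plan says.** Under Statistics, the protocol article states: "The main analysis will be a comparison of the proportions of abstinent smokers in the intervention and control groups". The method follows: "We will use chi-square tests and odds ratios with 95% confidence intervals to compare these proportions". The next sentence makes this conditional: "If covariates are needed due to imbalance despite randomization, we will use multivariate logistic regression models instead". Its last word makes the logistic model a replacement for the main analysis, not a sensitivity analysis beside it.

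The Sample size calculation rests on the unadjusted comparison: "a difference between quit rates of 10% in the control group and 17% in the intervention group", with "odds ratio = 1.84, power = 80"%, in two arms of 400.

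The baseline questionnaire collects likely predictors of abstinence from every participant, among them "Smoking status, cigarette consumption, level of tobacco dependence", and also age, sex, schooling, motivation and past quit attempts. The Objectives section names several of these, but only for the secondary question of who benefits. They are not named as adjustment variables for the primary comparison.

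**The concern.** After proper randomisation, any baseline difference between arms is chance. A covariate deserves adjustment because it predicts the outcome, not because it happens to differ between arms. A trigger based on imbalance can bring in a variable of no prognostic value and leave out a strong one that happens to be balanced.

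Two things are at stake. First, nobody can say beforehand which test will give the trial's single primary result. Second, the odds ratio is non-collapsible: for the same pair of quit rates, the odds ratio adjusted for prognostic covariates (conditional) lies further from 1 than the unadjusted one (marginal), even with perfect balance. The trigger therefore also changes what the reported number means. The sample size was calculated for the unadjusted version only.

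**Working it through.** **1. The plan's own figure.** Inputs from Sample size calculation: p₀ = 0.10, p₁ = 0.17, α = 0.05, power 80%. Sidedness is not stated; two-sided is assumed.

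- Odds ratio: (0.17/0.83) / (0.10/0.90) = 1.843, agreeing with 1.84.
- Uncorrected n per arm: [1.96·√(2·0.135·0.865) + 0.8416·√(0.10·0.90 + 0.17·0.83)]² / 0.07² = (0.947 + 0.405)² / 0.0049, which rounds up to 373 (746 in total).
- With continuity correction: (n/4)·[1 + √(1 + 4/(n·0.07))]² gives 401 per arm, 802 in total, against the stated 800.

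The stated size is reproduced as an unadjusted two-proportion calculation. At 400 per arm, power without the continuity correction is 82.7%.

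**2. How often chance would trigger the switch.** The document gives no threshold. Assume imbalance means P<0.05 on a baseline test and that the k covariates are independent. Then P(at least one) = 1 − 0.95^k.

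| k | Chance of a switch |
|---|---|
| 3 | 14% |
| 6 | 26% |
| 9 | 37% |
| 14 | 51% |

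Correlated covariates, such as dependence and cigarettes per day, would lower these figures.

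**3. What the switch does to error rates, power and the odds ratio.** Simulation: 6,000 trials per scenario, 400 per arm, control rate 10%, six independent standard-normal baseline covariates. The rule was to adjust for every covariate with baseline P<0.05, and otherwise to use the chi-square. The number and strength of the covariates are assumptions. The Monte Carlo standard error of the type I error is about 0.3 points.

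| Quantity | Log-OR 0.2 per SD | Log-OR 0.4 per SD |
|---|---|---|
| Trials that switch (null scenario) | 26.2% | 27.0% |
| Type I error, unadjusted | 5.0% | 4.7% |
| Type I error, always adjusted for all six | 4.8% | 4.5% |
| Type I error, imbalance rule applied mechanically | 4.8% | 4.4% |
| Type I error, better of unadjusted and fully adjusted | 5.7% | 6.1% |
| Power at 10% vs 17%, unadjusted | 83.6% | 83.2% |
| Power, always adjusted | 84.5% | 86.8% |
| Power, imbalance rule | 83.5% | 83.7% |
| Conditional OR equivalent to 10% vs 17% | 1.88 | 1.98 |

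Allowing for variation between simulation runs, the type I error from picking the better result is about 5.5% to 6.7%.

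**4. Where the power gain comes from.** The standard error of the log odds ratio does not fall with adjustment. It rises from 0.215 to between 0.220 and 0.230 over the strengths examined. Power increases only because the conditional odds ratio lies further from 1. The imbalance rule captures almost none of this gain.

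**The case against.** The strongest reply has four parts.

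- **The trigger concerns baseline data, not outcomes.** This stands. A reader might infer that the rule lets the primary test be chosen with the results in view, or that it inflates the false-positive rate. The text does not say so, and the mechanical rule ran at 4.4% to 4.8%. Inflation appears only if someone compares the unadjusted and adjusted results and reports the better one. The sentence does not exclude this, and the trial is open-label, but it does not plan it either.
- **A protocol article may leave the imbalance criterion and covariate list to a fuller document.** This also stands, so their absence is not part of the point. But a fuller document could only define the trigger. It could not remove it without contradicting the sentence printed here.
- **Fixed adjustment is not free precision.** Correct. A reader might assume that adjustment narrows the interval; in a logistic model the standard error rises slightly. The benefit is a small gain in power, tied to a different estimand.
- **The unadjusted test matches the sample size and is the smaller change.** This is fair. Keeping it as the primary analysis is an acceptable repair.

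None of this rescues the replacement rule itself.

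**Conclusion.** The point holds in a limited form. As written, chance imbalance decides which test is primary and whether the odds ratio is marginal or conditional. That is a defect in what the article states, not in what it leaves out. It should be corrected because it touches the primary result, but it does not invalidate the design.

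The switch could plausibly occur in anything from about one trial in seven to one in two, depending on how many covariates are inspected. That range rests on an assumed P<0.05 criterion and on independence. The shift in the target odds ratio, from 1.84 to about 1.88 to 1.98, rests on six covariates of assumed strength. The documents do not support a claim that the stated rule raises type I error.

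**What to change.** Delete the imbalance trigger and name one primary analysis that applies whatever balance is observed.

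- **Preferred:** logistic regression of the primary outcome on arm plus a short fixed list of prognostic baseline variables already collected, for example dependence, cigarettes per day, motivation, age, sex and education. Report the chi-square and the unadjusted odds ratio as supportive. Under the assumed covariate strengths, power at 800 is about 1 to 4 points higher than unadjusted.
- **Also sufficient:** keep the chi-square and unadjusted odds ratio as primary, with the fixed adjusted model as a sensitivity analysis.

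In either case, state whether the reported odds ratio is conditional or marginal. If the adjusted model is chosen, its odds ratio will not correspond to the 1.84 in the Sample size calculation, so the unadjusted rates and odds ratio should be shown beside it.

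The cost is a change of wording, made before outcomes by arm are examined. No new data are needed and the sample size stays at 800.
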